### Outcome measures

There will be two primary outcome measures: a change in cooking confidence (self-efficacy) and a change in self-reported mean vegetable intake (serves per day). Secondary outcome measures will include change in self-reported measures of: (i) mean daily fruit intake, (ii) mean weekly takeaway/fast food intake, (iii) frequency of cooking the main meal from basic ingredients, (iv) nutrition knowledge, (v) attitudes towards cooking, (vi) willingness to try new foods and (vii) enjoyment and satisfaction of cooking. Change in psycho-social measures such as (viii) global self-esteem and (ix) social connectedness in relation to cooking and eating will be measured as will (x) a change in participant’s total expenditure on food.

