Participant attitudes towards cooking and eating healthy foods, willingness to try new foods, enjoyment and satisfaction in cooking and eating healthy foods will be tested, using Likert scale based questions. Questions about shared enjoyment of cooking, eating and normative eating behaviours were adapted from questions from The Stephanie Alexander Kitchen Garden Evaluation (SAKG) [25]. The Rosenberg Self-Esteem Scale (RES), a widely validated and reliable measure of self-esteem, will also be administered [26]

Participants will be asked to report their total household food and drink (excluding alcohol) expenditure and expenditure specifically on take-away food and fruit and vegetables. Height and weight will be self-reported to enable the calculation of Body Mass Index (BMI).

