### Data analysis

Demographic and baseline characteristics will be summarised for both intervention and control groups using standard summary statistics (mean and standard deviation) and non-parametric statistics (medians and inter-quartile ranges) where applicable. Frequencies and percentages will be reported for categorical variables. The magnitude of change both within and between intervention and control groups for T1, T2 and T3 time-points will be assessed. For continuous data, such as fruit and vegetable intake, two sample t tests will be employed to compare means between intervention and control groups at each time point and paired t tests for within group comparisons. A split-plot in time Anova will be used as the basis for these t-tests. For categorical data, frequencies will be reported for intervention and control groups and chi squared analysis will provide between group comparison results. Regression analysis will be conducted to determine the potential contribution of specific demographic factors on the outcome variables of interest. All data analysis will be performed using STATA S.E. 12.0 statistical software.

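### For outcomes analysed as categorical, the only named test is a chi-squared comparison of group frequencies, which neither tests change from baseline nor, in its usual form, uses category order

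*Protocol article*

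**What the plan says.** The outcomes are defined as changes. For the primary pair, the Outcome measures section states: "There will be two primary outcome measures: a change in cooking confidence (self-efficacy) and a change in self-reported mean vegetable intake (serves per day"). The secondary outcomes are also introduced as changes in self-reported measures, among them "frequency of cooking the main meal from basic ingredients", attitudes, willingness to try new foods, and enjoyment. The Survey instrument section adds that "enjoyment and satisfaction in cooking and eating healthy foods will be tested, using Likert scale based questions".

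The quantitative Data analysis section opens with a general aim: "The magnitude of change both within and between intervention and control groups for T1, T2 and T3 time-points will be assessed". It then divides by type of data.

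- Continuous data: "two sample t tests will be employed to compare means between intervention and control groups at each time point and paired t tests for within" (the paired tests being for changes inside each arm). The section adds: "A split-plot in time Anova will be used as the basis for these t-tests".
- Categorical data: "For categorical data, frequencies will be reported for intervention and control groups and chi squared analysis will provide between group comparison results".
- Regression: "Regression analysis will be conducted to determine the potential contribution of specific demographic factors on the outcome variables of interest".

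The Study design section says that allocation follows program start date and is not randomised.

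**The concern.** Continuous outcomes get paired tests and a split-plot ANOVA, whose group-by-time term tests whether the two groups changed differently. Categorical outcomes get neither. The split-plot ANOVA is tied to the t tests, and the regression is described as a study of demographic factors, so no other sentence supplies a group-by-time or baseline-linked comparison.

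Two separate consequences follow for any outcome analysed as categories.

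1. **Change is not tested.** A table of group by response at T2 contains no baseline information. In a randomised trial that would mostly cost precision. Here the groups are defined by start date, and the Discussion relies on having pre and post measures to attribute change to the program. A T2 comparison sets the pre measure aside and can mistake a standing difference between groups for a program effect.
2. **Order is not used.** In its usual Pearson form, chi-squared treats ordered responses as unordered. It spends one degree of freedom fewer than the number of levels on any difference in shape, and its p value carries no direction. The first research question asks about an increase.

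**Working it through.** **The plan's own figure.** The only sample size stated is 250 per group for vegetable intake (0.5 serves a day, 80% power, 0.05 in the Sample size section). No SD or within-person correlation is given, so it cannot be reproduced, only back-solved. From n = 2·SD²·(1.960 + 0.842)²/δ², SD = √(250 × 0.25 / (2 × 7.849)) = 1.995 for the quantity compared. No power is stated for any categorical outcome. Below, 250 serves only as the group size, with two-sided 0.05 (sidedness is not stated in the article).

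**Step 1: what the named tests do.**

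| Data type | Within-person change | Change compared between groups |
|---|---|---|
| Continuous | paired t test | split-plot ANOVA (group by time) |
| Categorical | none named | none named; chi-squared on frequencies |

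**Step 2: baseline difference carried to T2.** Suppose there is no program effect and the groups differ at T2 by d SD because they differed by that much at baseline. d is an assumption, as the article gives no baseline data. For a 1-df comparison with n per group, the chance of p < 0.05 is Φ(d/√(2/n) − 1.960) + Φ(−d/√(2/n) − 1.960). With n = 250, √(2/250) = 0.0894.

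- d = 0.1: Φ(1.118 − 1.960) + Φ(−1.118 − 1.960) = 0.201
- d = 0.2: Φ(2.236 − 1.960) + Φ(−2.236 − 1.960) = 0.609

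The nominal rate is 0.05. These figures are for a 1-df test. If the same noncentrality (n·d²/2 = 1.25 or 5.0) is spread over the 4 df of a five-level Pearson test, the rates are 0.121 and 0.396: lower, but still well above 0.05.

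**Step 3: cost of ignoring order.** Take a pure trend that a 1-df ordered test detects with 80% power. The noncentrality is (1.960 + 0.842)² = 7.849. Pearson power is the probability that a noncentral chi-squared with K − 1 df and this noncentrality exceeds its 5% critical value.

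| Levels K | df | Pearson power | Loss against 80% |
|---|---|---|---|
| 3 | 2 | 70.9% | 9.1 points |
| 4 | 3 | 64.5% | 15.5 points |
| 5 | 4 | 59.5% | 20.5 points |
| 7 | 6 | 52.1% | 27.9 points |

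Simulated proportional-odds shifts with five levels (4,000 replicates per setting, 250 and 140 per group, three assumed baseline distributions) gave 58–63% for Pearson and 79–81% for the trend test. The loss also depends on the benchmark. With five levels and the ordered test at 70%, 90% or 95%, Pearson has 48.2%, 74.0% or 83.7%.

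**Step 4: does testing change cost power?** It can. With within-person correlation ρ and equal variances, a change score has variance 2(1 − ρ) in units of the T2 variance. Where the change test has 80% power, the T2-only test has Φ(2.802·√(2(1 − ρ)) − 1.960):

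- ρ = 0.3: 91%
- ρ = 0.5: 80%
- ρ = 0.7: 58%

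So the reason to test change is bias. Power can move either way.

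**The case against.** The strongest reply is that the affected outcomes are not identified. The article describes how items are presented, not how they are scored. The Sample size section mentions the missing standard deviation as one reason why cooking confidence could not be sized, which suggests a mean score. If Likert sets are summed or averaged, the t tests and split-plot ANOVA cover them. Fruit intake, takeaway intake and expenditure are quantities. That leaves main-meal cooking frequency as the plausible ordered category, and its response format is not given. This stands, and it limits the point to outcomes actually analysed as categories. A reader might infer that the primary confidence outcome is affected; the article does not establish that.

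A reader might also infer that the change questions for categorical outcomes go unanswered. The text does not support that either. The section states a general aim to assess change, frequencies by group show direction and size descriptively, and the type of chi-squared is left open: it could be a trend test, or be applied to categories of change.

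Finally, it can be said that an article leaves such detail to a fuller plan. That holds for scoring rules, but only in part for the test. The article does state a method for categorical data, and gives continuous data a baseline-linked analysis in the same paragraph. Followed as written, the stated method does not match the stated outcome.

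**Conclusion.** The point holds for outcomes analysed as categorical: plausibly cooking frequency, and any Likert item not scored as a continuous scale. For these, the named comparison does not test the change that defines the outcome. In a non-randomised design it can report a baseline difference as a result, in about 20% or 61% of studies for a 1-df test under an assumed carried-over difference of 0.1 or 0.2 SD. This is the main reason to act.

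The loss from ignoring order is a separate and secondary matter: 9 to 28 points of power for 3 to 7 levels, assuming a pure trend, the Pearson form and an ordered test at 80%. It is tempting to say that the plan loses about 20 points. That figure belongs to a five-level item under those assumptions. Five levels are stated only for the confidence items, and the article states no power for any categorical outcome from which points could be lost. The figure also says nothing about the cost of ignoring baseline.

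The change should be made, but the outcomes clearly at risk are secondary and their number is unknown.

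**What to change.** 1. State which outcomes are treated as categorical and which Likert sets are scored as continuous. The latter stay under the split-plot ANOVA.
2. For ordered categorical outcomes, replace the chi-squared comparison with a proportional-odds model for repeated answers (GEE or a random person effect) with group, time and group-by-time. For two-category outcomes use the logistic version.
3. Report the group-by-time odds ratio at T2 with its 95% CI as the between-group result. Controls have no T3 survey, so this contrast stops at T2.
4. Keep chi-squared for describing baseline characteristics.

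The cost is analysis wording and some programming. No new data are needed, and because the Sample size section rules out analysis before accrual closes, the change can be fixed before results are seen. There are two downsides. The proportional-odds assumption must be checked, and a group-by-time contrast can have less power than a T2-only test when within-person correlation is low (80% against 91% at a correlation of 0.3).

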### Qualitative study

### Research questions

To further understand how and why the JMoF program impacts on participants, the qualitative investigation will explore the following:

1. What are the expectations and experiences of participants?

2. What are the moderators, facilitators and barriers to behaviour change?

3. Were there any unanticipated outcomes?

### Study design

A longitudinal design will be employed for the qualitative study to follow program participants over the course of their JMoF journey. This will allow for prospective accounts of a participant’s experience and change over time [31,32]. Repeated semi-structured interviews will be conducted with participants. Up to three interviews will be conducted - prior to program commencement, on program completion and six months after completion.

### Participant interviews

The interview structure was generated to capture participant perspectives, to explore moderators, facilitators and barriers to behaviour change, and to capture any unanticipated outcomes from program involvement. As indicated in Table 1, the purpose of the sequential interviews is to understand participant expectations and experiences at different stages of program involvement. The interviews will be unstructured; however questions and prompts will be used to guide the discussion where appropriate. Table 1 lists the general discussion points used for each participant (interviews three and four will be based on previous discussions).

**Table 1 T1:** Interview structure

**Interview timing**	**Discussion topics**
Interview 1: Prior to commencement of the program	Motivations for registering for the program, expectations of the program. Discussion of previous and current food and cooking experiences.
Contact: During program	Phone conversation to recruit participants to repeat interviews and to enquire how the course is going.
Interview 2: After program completed	Discussion around their program experience and whether program expectations were met. If participants experienced any changes in food and cooking behaviour and any unanticipated changes as a result of the program.
Interview 3: Six months after program completion	Discussion around whether any changes as a result of the program have been sustained in terms of food and cooking behaviour. Any unanticipated changes as a result of the program. Reflection on what was talked about in the last interview.

Interviews of approximately 30-40 minutes duration will take place in a public location that provides a comfortable environment for both interviewer and the participant. All interviews will be conducted by the same researcher and participants will be required to consent to both participation and recording of the interview. To show appreciation for participation in an interview, participants will be thanked with a $15 Coles supermarket gift voucher at each interview.

### Participant sampling

Purposive sampling will be employed initially to capture maximum variation [33] in factors considered likely to influence expectations and experiences of the JMoF program. These factors were captured in the participant questionnaire and included socio-economic status, age, gender, family structure, and cooking confidence level. Further sampling will be informed by themes emerging from the initial interviews and instructor observations about characteristics that seem to influence participant motivations and experience. Interview one will subsequently be conducted with approximately 10-15 participants. Participants who provide rich data in terms of insights and unique perspectives, and who are willing to continue, will be invited to progress to interviews two and three. In the event that there are insufficient numbers to progress (less than 6), new participants will be recruited from new enrolments.

### Participant recruitment

Participants who have completed the baseline quantitative study survey and have agreed to be contacted for an interview, will be eligible to participate as well as all participants who are within the first three weeks of commencing the program. The baseline survey data will assist in purposive selection for the qualitative interviews, using the criteria based on demographic and personal circumstances as previously described. Opportunistic purposive sampling will also be carried out during the researcher’s time in Ipswich during class observations. Selected participants will be contacted by phone or in person (in class context) and provided with information about the qualitative component of the study and invited to participate in the interviews. Written consent will be required prior to participation in the interview process.

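### Interview 1 is defined as pre-program, but recruitment admits people up to three weeks into classes, so some expectations would be reported after exposure

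*Protocol article*

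**What the plan says.** Two places fix the timing of the first interview. The Study design section of the qualitative study schedules interviews "prior to program commencement, on program completion and six months after completion". Table 1, under Participant interviews, repeats it: "Interview 1: Prior to commencement of the program". The same table row lists the content as "Motivations for registering for the program, expectations of the program", followed by past and present food and cooking experience. The Interview 2 row returns to this material by asking whether expectations were met.

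The rationale for repeated interviews is given under Study design: "This will allow for prospective accounts of a participant’s experience and change over time".

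The Participant recruitment section then sets eligibility. It starts with people who completed the baseline survey and agreed to be contacted, and continues: "as well as all participants who are within the first three weeks of commencing the program". It adds a further route: "Opportunistic purposive sampling will also be carried out during" the researcher's class observation visits. Selected people may be approached in class as well as by phone.

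The Participant sampling section does not separate the routes: "Interview one will subsequently be conducted with approximately 10-15 participants".

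**The concern.** A person who is first approached after classes have begun cannot give an interview that precedes them. If the recruitment paragraph is followed as written, the set of first interviews may mix people who have not started with people who have attended one or more classes, while the plan treats them all as pre-program.

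This matters because the first qualitative research question asks about participants' expectations as well as their experiences, and because Interview 2 asks whether those expectations were met. For a late recruit, both would rest on expectations recalled with the classes already known. The account of current cooking in Interview 1 could also already reflect the program, though this is a weaker concern. The findings then feed the integrated analysis with the quantitative results.

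**Working it through.** The plan gives no figure on this point to reproduce. The check is a comparison of sections, with one small calculation of possible exposure.

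**Sections side by side**

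| Section | What it fixes |
|---|---|
| Study design (qualitative) | First interview before the program |
| Participant interviews, Table 1 | Interview 1 before the program; topics include expectations |
| Participant sampling | About 10-15 people receive interview one; no distinction by route |
| Participant recruitment | Eligible: consenting survey respondents, and also people in their first three weeks of the program; recruitment possible in class |

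The three-week clause could in principle be misread as referring to weeks before the start. Recruitment during class observations and contact in class rule that out, since both presuppose that classes are running.

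The sections from the qualitative research questions to the integrated analysis do not say that late recruits skip Interview 1, receive a different version of it, or are handled separately.

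**Possible exposure before Interview 1**

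- Inputs, from the description of the program in the Background: 10 weekly classes of 1.5 hours. From Participant recruitment: a window of three weeks.
- Classes: 3 weeks × 1 class per week = 3 of 10, which is 30%.
- Hours: 3 × 1.5 = 4.5 of 10 × 1.5 = 15, again 30%.

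This is the exposure at the end of the recruitment window. It assumes that every class is attended and that the interview follows recruitment without delay; the article does not give an interview date for these people.

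**Share of interviewees affected**

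No section limits or predicts how many of the 10-15 come by the in-program route. The range the article allows is 0 of 10-15 to all 10-15, so no percentage can be derived from it.

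**Which content depends on a pre-program interview**

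- Expectations: yes, directly.
- Current food and cooking experience: partly.
- Motivations for registering and previous cooking experience: no; everyone recalls these, including people interviewed before class one.
- Change in food and cooking behaviour: Interview 2 asks participants about it directly, so it is not derived by subtracting an Interview 1 measure.
- Moderators, facilitators and barriers, and unanticipated outcomes: no.

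**The case against.** The strongest reply is that this is a wording mismatch with little consequence. Purposive sampling is meant to be flexible, most recruits may come through the baseline survey, and interviewer memos already record context. The schedule also speaks of up to three interviews, so a late recruit might have fewer. Details of labelling late interviews are the kind of thing an article leaves to the full protocol.

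Part of this stands. The absence of a labelling rule would not be a finding by itself. But flexibility about whom to sample does not make an interview held after the start a pre-program one, and the clash lies in the article's own current text. Nor does the article say that late recruits enter at Interview 2; Participant sampling describes progression from interview one to two and three.

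Three stronger readings are tempting and are not supported:

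- A reader might infer that the prospective design fails for late recruits. It does not: their interviews at completion and six months are still prospective follow-up. What they lack is the pre-program account.
- A reader might infer that late entry shrinks the apparent change at Interview 2. Change is the participant's own account, analysed thematically, and nothing in the plan shows a direction of bias.
- A reader might attach a percentage to the affected sample. Any such figure would rest on assumed counts of late recruits.

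It is also fair to object to simply barring late recruits. Intervention participants are first surveyed at program commencement, and that survey informs selection. Requiring survey, selection, contact, consent and interview all before the first class could leave very little time.

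**Conclusion.** The inconsistency is real. Interview 1 is defined as pre-program in two places, and the eligibility paragraph admits people for whom that is impossible. Under the assumptions above, such a person could have had up to about 30% of the program before describing expectations.

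The reach is limited to one topic of Interview 1 (with a lesser effect on current cooking) and to the Interview 2 comparison that uses it. Within that reach it bears on the first qualitative research question, so it is worth correcting. Both primary outcomes, the sample size and the quantitative analysis are unaffected, as are people interviewed before their first class.

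**What to change.** Reconcile the Study design section, Table 1 and the Participant recruitment section:

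1. State that Interview 1 takes place before the program or, for late recruits, early in it.
2. Record at Interview 1 the number of classes already attended. This should be noted at the time, since later reconstruction would be less reliable.
3. Label interviews held after the first class as early-program.
4. Report pre-program expectation themes, and the Interview 2 comparison with them, only from participants interviewed before their first class. Keep late recruits in all other themes, including change.

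The cost is a few changed sentences and one recorded item per interview, and the recruitment pool is kept whole. The downside is that the expectation themes rest on fewer than the full 10-15 interviews, by however many late recruits there are. That number should be reported with the themes.
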